#### Adjustments

All analyses will be adjusted for the stratification variables (“center” and “pharmaceutical treatment at baseline”), and the outcome variable value will be assessed at baseline.

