### Inclusion criteria

Children are included if the following inclusion criteria are fulfilled: ADHD diagnosis after DAWBA interview [60] and verification with clinical interview K-SADS, ADHD section parent interview [62]; age between 6 and 13 years, both inclusive; the patient has access to a computer and the internet; and informed consent.

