### Statistical plan and data analysis

#### Sample size

We are planning a trial of a continuous response variable, “CANTAB RVP probability of hit,” from an independent control, and experimental participants will be allocated at a 1:1 ratio. In a pilot project ([name] et al., unpublished data), adolescents with ADHD played a set of games from Scientific Brain Management for 7 weeks. Here, the “CANTAB RVP probability of hit” was normally distributed, with a standard deviation (SD) of 0.22 points. If the true difference in the experimental and control mean is 0.13 points, we will need to include 61 experimental participants and 61 control participants to be able to reject the null hypothesis that the population means of the experimental and control groups are equal with a probability (power) of 90 %. The type I error probability associated with this test of this null hypothesis is 5 %. We will thus include 122 participants in total.

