#### Multiplicity and significance

For all outcomes, we will present the test statistic and the corresponding *P* values for exploratory purposes.

The purpose of the analysis of the secondary outcomes is to make additional claims of treatment benefits in addition to those already established by the analysis of the primary outcome. Consequently, multiplicity adjustments are needed. Multiplicity adjustments generally require a strong control of the familywise error rate. With regard to this, a useful approach is the gatekeeping approach [71], which we will apply in this trial.

There is one primary and four secondary outcomes. Thus, the primary outcome will be the gatekeeper of the family of secondary outcomes. The sample size has been estimated using a risk of type I error (alpha) of 0.05. The primary outcome will consequently be analyzed and interpreted according to a two-sided significance level of *P* ≤ 0.05. Thus, if P of the test of the primary outcome is ≤ 0.05, the primary outcome is assessed as statistically significant. In this case, we will use Hommel’s procedure, which is uniformly more powerful than the Holm as well as the Hochberg adjustment procedures. This means that the alpha of 0.05 can be transferred to the secondary outcomes that will be tested in a pre-specified sequence at the 0.05 level of significance (see sequence in Table 2). The approach requires that as soon as the *P* value of a test is > 0.05, the null hypotheses of the remaining secondary outcomes are accepted regardless of the test statistics.

If *P* of the test of the primary outcome is > 0.05, the primary outcome is assessed as statistically insignificant. Consequently, the trial result is insignificant, and all the null hypotheses of the four secondary outcomes will be accepted regardless of the test statistic.

All exploratory outcomes and exploratory analyses of the primary and secondary outcomes will likewise be subject to statistical tests. However, if P of the test is ≤ 0.05, the outcome will not be assessed as statistically significant due to multiplicity and the increased risk of a type I error. Likewise, if P > 0.05, we cannot assess the outcome as statistically insignificant due to a potential lack of power. All exploratory analyses will thus be strictly hypothesis generating.

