#### Subgroup analyses

For the primary and secondary outcomes, we will perform subgroup analyses according to age. We will divide the participants into two age groups of children aged 6 to 9 years or 10 to 13 years. We will perform a test of interaction to assess whether the effect of the intervention is different among the younger children compared with the older children. If *P* of the test of interaction is ≤ 0.05, we will present separate estimates for the two subgroups. As the randomization procedure was not stratified by age and we most likely will have reduced power for this analysis, the result is exploratory and strictly hypothesis generating.

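### Age is missing from the fixed covariate set for a 6-to-13-year sample; adding it is an optional, low-cost gain in precision, not the repair of an error

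*Protocol article*

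**What the plan says.** The Adjustments section opens with "All analyses will be adjusted for the stratification variables" and names these as centre and pharmaceutical treatment at baseline. The rest of the sentence brings in the outcome's baseline value. Read literally, it says only that this value is measured; it is presumably meant as a covariate. Age does not appear.

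Elsewhere in the protocol article:

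- Inclusion criteria: "age between 6 and 13 years, both inclusive".
- Randomization: the strata are trial site and medication use. Age is also not on the list of characteristics to be compared between arms.
- Subgroup analyses: "As the randomization procedure was not stratified by age" is given as one reason to treat the comparison of ages 6 to 9 with 10 to 13 as exploratory.
- Missing values: auxiliary variables are drawn from the outcomes, so age does not enter the likelihood model by that route.

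**The concern.** The sample covers eight year-groups of childhood. If age predicts the end-of-treatment score beyond what the baseline score already tells, its variance stays in the error term of the primary and secondary models. A chance difference in mean age between the arms would then be removed only to the extent that the baseline score carries it.

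What is at stake is some precision and some protection against an unlucky allocation. This counts for more if the trial stops short of 122 children, which the Sequential analysis section foresees, because chance imbalances widen as the sample shrinks. The secondary outcomes also have less room: Table 2 gives them 59 % to 78 % power.

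**Working it through.** **Inputs from the protocol article.** Target difference: "If the true difference in the experimental and control mean is 0.13 points". Pilot result: "with a standard deviation (SD) of 0.22 points". Alpha is 0.05 and two-sided (Sample size; Multiplicity and significance). Power is 90 %, with 61 children per arm.

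**Inputs assumed, because the article does not give them.** Correlation of age with the outcome, taken as equal at baseline and end: a = 0.2 to 0.6. Correlation of baseline with end value: r = 0.5 to 0.8.

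**1. The plan's own figure.** n per arm = 2 × (1.96 + 1.2816)² × (0.22/0.13)² = 2 × 10.51 × 2.864 = 60.2, so 61. This matches. Power at 61 per arm is 90.4 % (normal) or 89.9 % (noncentral t). The calculation uses the marginal SD with no covariate gain, so age plays no part in it. Table 2 also reproduces: 59.0 % and 78.2 % for 0.5 SD (noncentral t).

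**2. Precision.** Residual variance with baseline only is 1 − r². Adding age cuts it by the fraction a²(1 − r) / [(1 + r)(1 − a²)].

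| a | r = 0.5 | r = 0.6 | r = 0.7 | r = 0.8 |
|---|---|---|---|---|
| 0.2 | 1.4 % | 1.0 % | 0.7 % | 0.5 % |
| 0.3 | 3.3 % | 2.5 % | 1.7 % | 1.1 % |
| 0.4 | 6.3 % | 4.8 % | 3.4 % | 2.1 % |
| 0.5 | 11.1 % | 8.3 % | 5.9 % | 3.7 % |
| 0.6 | 18.8 % | 14.1 % | 9.9 % | 6.2 % |

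Fifteen of the 20 cells lie below 6.5 %. The model already has six parameters (intercept, treatment, two for centre, medication, baseline), so one more covariate costs about 1/(122 − 6) = 0.9 % of variance. Two cells fall below that and show no net gain. If the age correlation at the end equalled r times that at baseline, age would add nothing at all.

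**3. Power with baseline in the model**, ignoring the cost of the extra covariate:

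| Outcome | r | Without age | With age |
|---|---|---|---|
| Primary, 0.13 | 0.5 | 96.5 % | 96.7 % to 98.7 % |
| Primary, 0.13 | 0.7 | 99.55 % | at most 99.8 % |
| Secondary, 0.5 SD, alpha 0.05 | 0.5 | 89.0 % | 89.5 % to 94.3 % |
| Secondary, 0.5 SD, alpha 0.05 | 0.7 | 97.2 % | 97.3 % to 98.3 % |

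**4. Chance imbalance.** The standard error of the arm difference in mean age is √(2/61) = 0.181 SD, with 95 % of differences within ±0.35 SD. The chance of exceeding 0.2 SD either way is 27 %. If ages were spread evenly over 6 to 13 (assumed; SD 2.29 years), the standard error is 0.41 years and the 95 % limit 0.81 years.

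The expected shift in the primary difference at a 0.2 SD imbalance is:

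- No baseline adjustment: a × 0.2 × 0.22 = 0.009 to 0.026.
- Baseline adjusted: a × (1 − r) × 0.2 × 0.22 = 0.002 (a = 0.2, r = 0.8) to 0.013 (a = 0.6, r = 0.5), which is about 1 % to 10 % of 0.13.

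On these assumptions, baseline adjustment removes a share r of the imbalance effect, here 50 % to 80 %.

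**The case against.** The strongest reply is that nothing is wrong. Adjusting for the stratification variables and the baseline outcome is a conventional, valid pre-specified set. Omitting a further prognostic variable does not bias the estimate under randomisation or inflate type I error. Chance imbalance is already reflected in the standard error, and further covariates are often left to an analysis plan, which is not shown here. All of this stands, except that the Adjustments section speaks of all analyses and so fixes the set instead of deferring it.

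Four stronger readings are tempting but lack support:

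- A reader might infer that the trial is underpowered without age. It is not: the 61 per arm assumes no covariate gain. It is equally wrong to credit age with lifting power from 90 %, because the planned baseline adjustment comes first and already raises power.
- A reader might infer that the trial itself expects age to predict the outcome. The Cognitive training, Objectives and Subgroup analyses sections ask whether younger children benefit more. That is effect modification, for which an interaction test is already planned.
- A reader might infer that the baseline test is too noisy to carry the age effect. The article says nothing of the kind; the Primary outcome section credits the battery with sound psychometric properties.
- A reader might see a fault in the interaction model containing age when the primary model does not. Any interaction model for an unstratified factor adds that factor's main effect, and this one is labelled exploratory.

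**Conclusion.** The point holds as an optional improvement. Age is absent from the fixed set, is not a stratifier and has no other route into the primary model. Precision may be lost, but the article gives no figure that shows it is. The likely cut in residual variance is a few percent, within a range from no net gain to about 19 %, and it rests wholly on the assumed correlations. The residual effect of a 0.2 SD age imbalance is 1 % to 10 % of the target difference. That figure presumes the baseline outcome really is a covariate; if the loose sentence in Adjustments meant otherwise, it would be about 7 % to 20 % (0.009 to 0.026 out of 0.13). Validity, type I error and the planned 90 % power are intact.

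**What to change.** Before unblinding, pre-specify age in years as a continuous covariate in the models for the continuous outcomes, next to centre, baseline medication and the baseline outcome. In the same edit, state plainly that the baseline outcome is a covariate.

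The cost is one degree of freedom and one line of text. No new data are needed, since age is established for eligibility. The downside is that there may be no net gain if age adds little beyond baseline. The change does not reach the non-parametric fallback in the Analytical model section, which stratifies by centre only. Trial status reports recruitment as ongoing and Blinding provides for coded analyses, so the covariate can be fixed now without appearing data-driven.

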#### Missing values

In the analysis of the continuous variables, structural equation models (for example, “proc calis” in SAS 9.3) that include the direct maximum likelihood method (full information likelihood) will be used. Applying this method implies that unbiased estimates of the regression parameters will be obtained as long as the values are only missing at random. To improve the efficiency, all auxiliary variables present among the outcomes will be added to the model. An auxiliary variable is defined as a variable not in the analytical model but correlated (defined as |r| > 0.40) with one or more variables that 1) have missing values, and 2) are included in the analytical model. Thus, the auxiliary variables included may vary from one regression equation to the next one.

#### Sensitivity analyses

Best-worst and worst-best sensitivity analyses of the primary outcome will be done. Here, missing values in one intervention group are imputed by the minimum value found in the total material (“best case”), and missing values in the other group are imputed by the maximum value found in the total material (“worst case”) and vice versa. The range of the estimates of the two regression parameters of the intervention indicator will convey an impression of the bias one may expect if values are missing not at random.

#### Per-protocol analyses

For the primary and secondary outcomes, we will use exploratory analyses to perform per-protocol analyses. Participants will be included in the intervention group, if they have complied with at least 20 out of the 48 scheduled computer training sessions. Participants will be included in the control group if they have not attended any computer training sessions.

#### Subgroup analyses

For the primary and secondary outcomes, we will perform subgroup analyses according to age. We will divide the participants into two age groups of children aged 6 to 9 years or 10 to 13 years. We will perform a test of interaction to assess whether the effect of the intervention is different among the younger children compared with the older children. If *P* of the test of interaction is ≤ 0.05, we will present separate estimates for the two subgroups. As the randomization procedure was not stratified by age and we most likely will have reduced power for this analysis, the result is exploratory and strictly hypothesis generating.

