### Cognitive training

Cognitive training is rooted in cognitive rehabilitation, based on the concept that direct training can result in a reorganization of neural functions. Among other effects, neuroplasticity allows the central nervous system to learn new skills, remember information and reorganize neural networks in response to external stimulation [33]. The basic mechanisms involved are neurogenesis, programmed cell death and activity-dependent synaptic plasticity [33]. Childhood is a period of changes in the brain’s anatomical structure and synaptic connections. A child’s brain is more susceptible to the environmental impact than the adult’s brain due to increased plasticity [33]. Thus, injuries and some neurological diseases are overcome by children faster and easier than by adults. Several studies indicate that the peak of brain plasticity is reached within the first 7 years of life [34], although the potential is likely to be lifelong. For example, a functional magnetic resonance imaging (fMRI) open trial of young healthy adults found that training working memory resulted in an increased brain activity in the dorsolateral, prefrontal, and parietal association cortex, indicating plasticity of the neural system [35]. These cortical areas are overlapping the prefrontal regions, which are likely implicated in the pathology of ADHD [36, 37]. Despite the hypothesis that children under the age of 7 have better neuroplasticity and therefore may benefit more from cognitive training as compared to older children, we have not identified any studies investigating the effect of cognitive training in different age groups.

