## Methods/Design

### Objectives

The primary objective is to investigate whether computer training with the games embedded in ACTIVATE™ (http://denmarkstudy2.c8sciences.com/?language=da) has a positive effect on specific cognitive functions. The secondary objectives are to investigate whether there is an effect on ADHD symptoms and functional outcome. Exploratory objectives are to investigate the effects at 12 and 24 weeks after training and to investigate whether younger children benefit more from training than older children.

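### The exploratory age analysis splits age at 9/10 without a stated reason and ties the subgroup estimates to a significant interaction; continuous age with unconditional reporting would serve the question better

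*Protocol article*

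**What the plan says.** The Objectives section of the protocol article lists, among the exploratory objectives, "to investigate whether younger children benefit more from training than older children". The rationale is in the Background under Cognitive training: the hypothesis that "children under the age of 7 have better neuroplasticity and therefore may benefit more from cognitive training as compared to older children".

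The Subgroup analyses section fixes the method for the primary and secondary outcomes. The bands are set as follows: "We will divide the participants into two age groups of children aged 6 to 9 years or 10 to 13 years". The test is a treatment-by-band interaction: "We will perform a test of interaction to assess whether the effect of the intervention is different among the younger children compared with the older" ones. The reporting rule is that if P "of the test of interaction is ≤ 0.05, we will present separate estimates for the two subgroups". No other condition for showing them is given, and no analysis of age as a continuous variable is mentioned. The section is candid about its limits: "we most likely will have reduced power for this analysis, the result is exploratory and strictly hypothesis generating".

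**The concern.** Two choices are stated here, and each could be better.

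- **The cut.** The article does not justify a boundary between 9 and 10. The only boundary it mentions is 7, and the objective speaks simply of younger and older children. A split at 9/10 treats a child of 6 like one of 9, and a child of 9 unlike one of 10. If benefit falls off gradually with age, the split wastes information in an analysis already acknowledged to be short of power.
- **The reporting gate.** Subgroup estimates are tied to P ≤ 0.05 on that weak test. A real age difference would then often leave no estimates in the report, and those that do appear would be selected for being large. The value of a hypothesis-generating analysis lies mainly in its estimates and intervals. The gate also sits badly with the section on Multiplicity and significance. That section says P > 0.05 in an exploratory analysis cannot be taken as evidence of no effect, because power may be lacking.

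**Working it through.** **Inputs from the article.** Age 6 to 13 inclusive (Inclusion criteria). SD 0.22, planned difference 0.13, 61 per arm and 122 in total, power 90%, alpha 5% (Sample size); two-sided (Multiplicity and significance); 1:1 allocation (Randomization).

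**Assumptions, because the article gives no figure.** The age distribution; the shape of the effect by age (linear unless stated); equal bands; no gain from baseline adjustment unless stated. Power uses the two-sided normal approximation.

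**1. The plan's own figure.** n per arm = 2 × [0.22 × (1.960 + 1.282) / 0.13]² = 60.2, rounded up to 61. The stated sample size reproduces. The article gives no power for the age interaction.

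**2. Information kept by the split.** For a linear trend this is the squared correlation between age and the indicator of age 10 or over.

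- Whole-year ages 6 to 13, evenly spread: the variance of age is 5.25. The band means are 7.5 and 11.5, so the variance between bands is 2² = 4. Kept: 4 / 5.25 = 0.762, a loss of 24%. That equals the information of about 93 of the 122 children.
- Near-normal ages split at the middle: kept 2/π = 0.637, a loss of 36%, or about 78 of the 122 children.
- If the effect steps exactly at 10: nothing is lost.

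**3. If the effect steps at 7, as the rationale suggests.** With even whole-year ages, the squared correlation of the under-7 indicator with the 9/10 band is 0.143, and with linear age 0.333. Neither isolates children under 7, but continuous age captures more of that contrast (33%) than the planned cut (14%).

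**4. Power for the interaction.** With four equal cells, SE = 0.22 × √(16/122) = 0.0797. For continuous age under the same linear trend with even ages, the noncentrality is divided by √0.762 = 0.873.

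| Difference in effect between bands | Noncentrality, banded | Power, banded | Power, continuous |
|---|---|---|---|
| 0.065 (half the planned effect) | 0.82 | 13% | 15% |
| 0.13 (the whole planned effect) | 1.63 | 37% | 46% |
| 0.22 (1 SD, about 1.7 times the planned effect) | 2.76 | 79% | 89% |

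The smallest band difference detectable with 80% power is (1.960 + 0.842) × 0.0797 = 0.22. A difference of 0.13 would need 16 × [0.22 × (1.960 + 0.842) / 0.13]² ≈ 360 children for 80% power.

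The article adjusts for the baseline value but gives no correlation. With an assumed correlation of 0.5, the SD falls to 0.22 × √(1 − 0.25), and power for 0.13 is 47% banded and about 58% continuous. With 0.7 it is 63% and about 74%. The proportional loss from banding is unchanged.

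**5. Effect of the reporting gate.** For a true difference of 0.13, banded and unadjusted, the estimates would not be shown in 100 − 37 = 63% of trials. That figure is 53% with a baseline correlation of 0.5 and 37% with 0.7. When they are shown, the interaction estimate is on average about 1.6 times the truth (unadjusted). For a true difference of 0.065 the exaggeration is about threefold.

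**The case against.** The best defence is that this is a prespecified, openly exploratory analysis. The article concedes low power, and the Multiplicity section says no exploratory result will be called statistically significant. A fixed split at the middle of the age range prevents searching for a cut-point, is easy to read, and answers a younger-versus-older question as worded. A cut at 7 would leave only about 15 of 122 children (122 / 8) in the young group if ages are even. Withholding subgroup estimates unless the interaction is significant is also a familiar guard against over-reading chance subgroup findings. Much of this stands, and it is why the point is minor. It does not supply a reason for 9/10, and admitting low power is no reason to reduce it further.

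A reader might infer more than the documents support:

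- **That a quarter of the information is lost as a matter of fact.** The figure needs a linear trend and evenly spread ages, and the article gives neither.
- **That a main objective is compromised.** The objective is exploratory and no confirmatory claim rests on it.
- **That continuous age would give a well-powered test.** This is roughly true only for differences near 1 SD. At the size of the whole planned effect, the unadjusted test stays below 50% with even ages.
- **That nothing is reported after a non-significant test.** The article does not use the word only, and it promises test statistics and P values for all outcomes, which may cover the interaction test. Tying the separate estimates to P ≤ 0.05 is still the plain reading.

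**Conclusion.** The point holds as a minor weakness in two stated choices. The 9/10 split is unexplained and does not match the under-7 rationale. Under a linear trend it costs between about 24% (even ages) and about 36% (near-normal ages) of the information, and it costs nothing if the effect steps at 10. For an interaction of 0.13, unadjusted power is about 37% with bands and about 46% with continuous age, so the analysis remains underpowered and exploratory under either method.

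The reporting gate is the stronger half, because the selection it causes depends on neither linearity nor the age distribution. At unadjusted power it would leave most real differences of 0.13 without published estimates and inflate those shown. A strong baseline correlation (0.7) would reduce the unreported share to about 37%. The primary conclusion of the trial is unaffected.

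**What to change.** In the adjusted model, include age as a continuous main effect and test treatment by continuous age. Report the interaction slope and the model-based treatment effects at a few prespecified ages, for example 7, 10 and 13, each with a 95% confidence interval, whatever the P value. Keep the 6 to 9 and 10 to 13 bands as a descriptive display, also shown with intervals whatever the P value, and keep the label hypothesis generating.

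The cost is about one line of the analysis plan and the matching code. Age is already needed for eligibility and for the bands, and trial conduct does not change. The small downside is the linearity assumption, which 122 children can check only weakly; the descriptive bands give a rough view of it.
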